#### Participants

The recruitment population is pregnant women presenting for their first antenatal visit at GUH and MGH at 12 to 18 weeks gestation. Participation in the study ends on completion of the pregnancy. All expectant mothers in Ireland are entitled to the Maternity and Infant Care Scheme, which consists of a shared programme of care provided by GPs in primary care and obstetricians in the hospital maternity units, or secondary care. The care scheme provides for an initial examination with the GP before 12 weeks gestation, followed by a hospital appointment and scan at 12 to 18 weeks gestation, followed by 6 further examinations alternated between the GP clinic and the maternity unit over the course of the pregnancy. Screening for GDM is embedded in hospital practice and supported by protocols.

#### Eligibility criteria

•Inclusion criteria: Women presenting with a pregnancy at GUH and MGH during the recruitment phase will be included.

•Exclusion criteria: Women with established diabetes or diagnosed GDM will be excluded.

#### Recruitment

Recruitment for the trial will be initiated at the woman’s first hospital visit at 12 to 18 weeks gestation. A list of all women with a confirmed pregnancy presenting at the obstetrics outpatient clinics at GUH and MGH will be obtained from the hospital databases by the principal investigator, who is a member of the clinical care team at both sites. Each woman will be sent an invitation letter, participant information leaflet and participant consent form in the post. The information will be followed up with a phone call to each woman to answer questions and obtain verbal consent before randomising those who consent to the primary care and secondary care screening groups. The baseline characteristic questionnaire will be administered at this time. The phone calls will be conducted by members of the research team. Each consenting woman will be asked to return the written consent form to the study office. For some of the participants (that is, those who meet the risk factor criteria for selective GDM screening), an appointment for an OGTT may have already been scheduled at their 12 to 18 week hospital visit. In such cases, researchers will continue the randomisation process as usual and inform the clinic if a change is required to the screening schedule. Those who were not selected for screening at the 12 to 18 week clinic but who consent to the study and are randomised into the secondary care screening group will be added to the hospital’s screening schedule. Outcome data will not be collected from participants who discontinue. The flow chart in Figure 1 represents the movement of a participant through the stages of recruitment.

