#### Sample size and power calculation

On the basis of a comparison of two proportions a sample of 784 is needed to have 80% power, at the 5% significance level, to detect a ≥10% change in screening uptake. To achieve the required sample size, 1,513 patients will be invited to participate in the RCT, as 74% recruitment and 30% patient attrition (seen in Atlantic DIP) is anticipated. Recruitment will continue until target sample size is reached.

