### Outcomes

#### Primary outcome: uptake of screening

The primary outcome in the RCT is uptake of screening in the primary care and secondary care settings. First, the number of screening offers accepted will be assessed by comparing the number of screens offered (via the obstetrics outpatient clinic list) with the number of offers accepted (via the randomisation schedule). Second the uptake rate will be determined by comparing the number of women randomised to each setting to the number of OGTTs performed in that setting (via the GUH and MGH laboratory records).

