### Analysis plan

Differences in patient characteristics in primary care versus secondary care will be presented using suitable numerical and graphical summaries. A nonlinear mixed model for a binomial response will be used to compare the proportion of uptake between those in primary and secondary care while adjusting for differences in patient characteristics at baseline as appropriate. The analysis of the secondary responses will involve linear and nonlinear mixed models for continuous and categorical responses and survival models for the analysis of time to event data. The main analysis will follow an intention-to-treat strategy; sensitivity analyses and per protocol analysis will be used to explore the effect of departures from the assumption made in the main analysis. All analyses will be performed using R Statistical advice and analysis will be provided by [name] of the HRB Clinical Research Facility, NUI Galway.

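### The protocol collects no outcome data from women who discontinue, which does not fit an uptake rate over all randomised women or an intention-to-treat main analysis

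*Protocol article*

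**What the plan says.** Four statements in the protocol article bear on this.

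- Recruitment: "Outcome data will not be collected from participants who discontinue". The article does not define discontinuation.
- Outcomes, primary outcome: the uptake rate comes from "comparing the number of women randomised to each setting to the number of OGTTs performed in that setting (via the GUH and MGH laboratory records". The denominator is women randomised, and the numerator comes from routine laboratory records.
- Analysis plan: "The main analysis will follow an intention-to-treat strategy", with sensitivity and per-protocol analyses for departures from assumptions.
- Sample size and power calculation: "a sample of 784 is needed to have 80% power, at the 5% significance level, to detect a ≥10% change in screening uptake", and "1,513 patients will be invited to participate in the RCT, as 74% recruitment and 30% patient attrition (seen in Atlantic DIP) is anticipated".

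The trial is unblinded (Abstract, Methods/Design). Women are randomised after verbal consent by telephone (Recruitment). Researchers book the secondary care test during the recruitment calls, whereas in primary care the GP is asked to contact the woman (Interventions). Some women already have a hospital OGTT booked before randomisation (Recruitment). A woman whose GP cannot perform the test is offered one in hospital (Setting).

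**The concern.** An uptake rate over all randomised women needs, for each of them, either an observed OGTT status or a stated rule that supplies one. The Recruitment sentence withholds the status, and no section supplies the rule.

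This matters more here than for most endpoints because leaving the trial and not being screened may be the same event. Allocation is open, the arms differ in location and in who books the test, and the Background reports that attendance falls with travel distance. Discontinuation could therefore depend on the arm. If it does, the handling of these women can shift the primary contrast by an amount comparable with the difference the trial is designed to detect. Uptake is also the effectiveness measure in the economic evaluation, so an error would carry over into the cost-effectiveness ratio.

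**Working it through.** **1. The plan's own figures.** The sample size section gives no base rate. I assume 44% (the Atlantic DIP uptake in the Background), a rise of 10 percentage points, a two-sided 5% test and 80% power.

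n per arm = [1.96√(2p̄(1−p̄)) + 0.84√(p₁(1−p₁) + p₂(1−p₂))]² / (p₂−p₁)²

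With p₁ = 0.44, p₂ = 0.54 and p̄ = 0.49 this gives 392 per arm, 784 in total. Invitations: 784 / (0.74 × 0.70) = 1,513.5. Both published figures reproduce.

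**2. What those figures imply.** 1,513 × 0.74 ≈ 1,120 recruited, and 1,120 × 0.70 = 784. If attrition follows randomisation, 784 is the number retained and about 336 randomised women (30%) leave the analysed sample. If women with no test simply stayed in the denominator as not screened, uptake would need no attrition allowance. The Abstract, however, describes 784 women offered screening, 392 per arm, which reads as the number randomised. In that case a 30% loss leaves 784 × 0.70 ≈ 549, and power for 44% v 54% is about 65%.

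**3. The statements side by side.**

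| Section | Implied handling of a woman who discontinues |
|---|---|
| Recruitment | Outcome not collected |
| Sample size | Probably lost from the analysed number |
| Primary outcome | In the denominator; any OGTT in that setting counted |
| Analysis plan | Analysed as randomised |

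The first two rows suggest an analysis of those who remain; the last two require all randomised women.

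**4. Effect of each handling.** Let u be true uptake among all randomised women in an arm, d the proportion who discontinue, and s the proportion of discontinuers who are in fact screened. The article gives none of these by arm, so every value below is an assumption.

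*Discontinuers dropped:* observed uptake = (u − ds) / (1 − d). This exceeds u whenever s < u. With s = 0 it is u / (1 − d).

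| True uptake, arm A v B | Loss, A v B | Observed, A v B | Observed difference |
|---|---|---|---|
| 50% v 50% | 30% v 20% | 71.4% v 62.5% | 8.9 points, spurious |
| 50% v 50% | 30% v 30% | 71.4% v 71.4% | none |
| 44% v 44% | 32.5% v 27.5% | 65.2% v 60.7% | 4.5 points, spurious |
| 44% v 44% | 35% v 25% | 67.7% v 58.7% | 9.0 points, spurious |
| 44% v 54% | 35% v 25% | 67.7% v 72.0% | true 10 points shrinks to 4.3 |

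First row: 0.50/0.70 = 0.714 and 0.50/0.80 = 0.625. With 560 randomised per arm (1,120/2), a two-sided 5% test of two proportions would reject a true null about 26% of the time in the third row and about 74% in the fourth. With equal loss and equal uptake it rejects 5% of the time.

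*Discontinuers kept in the denominator, records not read:* observed uptake = u − ds. The understatement at d = 30% runs from 0 (s = 0) to 30 points (s = 1). With 30% v 20% loss and the same s in both arms, the false difference is (0.30 − 0.20)s, from 0 to 10 points, now against the arm that lost more women.

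The two handlings therefore err in opposite directions, and the article does not say which applies.

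**The case against.** The strongest reply is that the primary outcome section already fixes the denominator as women randomised. On that reading a woman who discontinues without a test remains as non-uptake, nothing is deleted, and the analysis is intention-to-treat. An unseen analysis plan might say so.

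Part of this stands. A reader might infer that the main analysis cannot be intention-to-treat, that failures are removed from the denominator, and that uptake is overstated in both arms. The document does not support that as fact, for these reasons:

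- The stated denominator points the other way, and with records unread the error would be understatement.
- Because discontinuation is undefined, missing an OGTT is not equated with it. It could also cover pregnancy loss or moving away.
- Not every discontinuer need be unscreened, since some women already have a hospital test booked.
- The 30% attrition is taken from Atlantic DIP and is not explicitly placed after randomisation.
- Written consent forms are posted before the call. The article does not say whether they are returned before or after the woman learns her allocation, so that sequence cannot be relied on as the cause of loss.
- Loss rates by arm are assumed throughout.

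What does not stand is the claim that nothing needs changing. The all-randomised denominator still needs each woman's OGTT status, which the Recruitment sentence withholds, and the attrition allowance has little purpose if everyone stays in. An analysis plan can set a counting rule, but it cannot supply data that the protocol says will not be collected.

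**Conclusion.** The concern holds as an internal conflict about the primary outcome. The Recruitment sentence, the all-randomised denominator, the intention-to-treat statement and the attrition allowance cannot all apply as written. The attrition allowance suggests, without proving, that discontinuers leave the analysed sample.

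Neither the size nor the direction of any bias can be fixed from the document. If discontinuers are dropped and are less often screened than other women, uptake is overstated. A 10-point gap in loss can then produce a false difference of about 9 points, close to the 10-point target. If they are kept but their records are not read, uptake is understated by the tests they had. Loss that is equal in arms with equal true uptake distorts the level but not the comparison.

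The published 784 and 1,513 are arithmetically sound; what is unclear is whether 784 women are randomised or retained.

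**What to change.** Replace the Recruitment sentence with a rule to this effect: OGTT status is taken from the GUH and MGH laboratory records for every randomised woman, including those who discontinue, unless she withdraws permission to use her records; all randomised women are analysed in their allocated arm, and a woman with no OGTT on record is counted as not screened.

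Alongside it:

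- Define discontinuation.
- State whether an OGTT done outside the allocated setting counts as uptake, consistently with the primary outcome section, which counts tests in that setting. Report the other definition as a sensitivity analysis. This matters because the Setting section provides a hospital test when a GP cannot perform one.
- Report women who withdraw record permission by arm, with sensitivity analyses counting them as not screened, as screened, and excluded.
- State whether 784 is the number randomised or retained, and align the Abstract and the sample size section.

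The cost is a wording change to the protocol and the participant leaflet, submitted to the ethics committee and registries as the Study management section requires, plus a record look-up already done for the other women. It depends on consent covering these records, which the article does not describe.

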**Figure 1 F1:**
[figure not shown]
Participant flow through recruitment process.

#### Sample size and power calculation

On the basis of a comparison of two proportions a sample of 784 is needed to have 80% power, at the 5% significance level, to detect a ≥10% change in screening uptake. To achieve the required sample size, 1,513 patients will be invited to participate in the RCT, as 74% recruitment and 30% patient attrition (seen in Atlantic DIP) is anticipated. Recruitment will continue until target sample size is reached.

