**Methods/Design:**

This will be an unblinded, two-group, parallel randomised controlled trial (RCT). The target population includes 784 women presenting for their first antenatal visit at 12 to 18 weeks gestation at two hospitals in the west of Ireland: Galway University Hospital and Mayo General Hospital. Participants will be offered universal screening for GDM at 24 to 28 weeks gestation in either primary care (n = 392) or secondary care (n = 392) locations. The primary outcome variable is the uptake rate of screening. Secondary outcomes include indicators of clinical effectiveness of screening at each screening site (primary and secondary) including gestational week at time of screening, time to access antenatal diabetes services for women diagnosed with GDM, and pregnancy and neonatal outcomes for women with GDM. In addition, parallel economic and qualitative evaluations will be conducted. The trial will cover the period from the woman’s first hospital antenatal visit at 12 to 18 weeks gestation, until the completion of the pregnancy.

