In terms of screening, for example, professional groups disagree on whether to recommend universal or selective screening (based on risk factors) [12,18,19]. While some studies have found that universal screening for GDM is superior to risk factor-based screening in terms of number of cases detected, time to diagnosis and treatment, and improved pregnancy outcomes [20,21], others have found no such effects. For example, a review of four trials comparing universal and selective screening, found that there is little high-quality evidence on the effects of screening for GDM on health outcomes for mothers and their babies. The paper concluded that further research is required to see which recommendations for screening practices for GDM are most appropriate [22].

Additionally, the site of screening is likely to be important, both in terms of the location of the screen (regional versus local) and in terms of the provider of the screening service (GP versus hospital). For example The Atlantic DIP study, which offered universal screening to all pregnant women, recorded an uptake rate of only 44% [17]. Follow-up analysis to explain this low screening uptake rate revealed that travel distance to the hospital screening site is an important factor in determining uptake rates [23]. Specifically, the probability of attending for screening is 15% lower for a patient who lives 50 kilometers from a screening centre, compared to an otherwise similar patient who lives closer to the hospital. The corresponding reduction in the probability of attending for an individual residing 100 kilometers away is 30%. This suggests that the availability of GDM screening in local (primary care) settings could result in higher uptake rates; however, this has not been empirically tested to date.

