### Hypothesis

The formal null hypothesis to be tested in this study is that there is no difference in uptake of screening for GDM amongst women randomised to primary care screening compared to women randomised to secondary care screening.

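### 784 serves both as the number allocated and as the number left after 30% attrition, so the randomisation target (784 or about 1,120) is not fixed

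*Protocol article*

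**What the plan says.** The sample-size section of the protocol article states that "a sample of 784 is needed to have 80% power, at the 5% significance level", and that this is "to detect a ≥10% change in screening uptake". It then gives the route to that number: "To achieve the required sample size, 1,513 patients will be invited to participate in the RCT, as 74% recruitment and 30% patient attrition" is expected. It closes with "Recruitment will continue until target sample size is reached".

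The abstract (Methods/Design) attaches 784 to women at their first antenatal visit, who will be offered screening "in either primary care (n = 392) or secondary care (n = 392) locations".

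Three other places bear on who is counted:

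- The Recruitment section says that women who discontinue will have no outcome data collected.
- The primary-outcome section sets the number of tests performed, taken from laboratory records, against the number of women randomised to each setting.
- The Analysis plan makes intention-to-treat the main analysis.

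**The concern.** The same figure is used at two different stages of the trial. In the sample-size section 784 is what is left after attrition. In the abstract it is what is allocated, before any attrition. The intermediate figure of about 1,120 randomised, which the invitation count requires, is printed nowhere. The rule for ending recruitment refers to a target sample size without saying whether that means women randomised or women retained. Staff could therefore stop at 784 or at about 1,120 and claim to have followed the protocol.

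The sections also disagree on whether attrition removes women from the primary analysis. The inflation and the rule on discontinuers say that it does. The outcome denominator and intention-to-treat say that it does not. Whether the stated power is met, exceeded or missed depends on how these two questions are answered together.

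**Working it through.** **Inputs.** Total 784, power 80%, significance level 5%, a change of 10%, 74% recruitment, 30% attrition and 1,513 invitations (sample-size section); 392 per arm (abstract). The level is taken as two-sided because the null hypothesis is that "there is no difference in uptake of screening for GDM amongst women randomised to primary care screening" compared with secondary care. The calculation states no reference uptake rate. The only one in the document is in the Background, where a previous regional study "recorded an uptake rate of only 44" per cent.

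**1. Reproduce 784.** Pooled-variance formula for two proportions, no continuity correction:

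n per arm = [1.96·√(2p̄(1−p̄)) + 0.842·√(p₁(1−p₁)+p₂(1−p₂))]² / (p₁−p₂)²

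- 45% vs 55%: [1.96 × 0.7071 + 0.842 × 0.7036]² / 0.01 = 391.3, so 392 per arm and 784 in total.
- 44% vs 54%: 391.1, so 784 again. 46% vs 56% gives the same by symmetry.
- Maximum-variance shortcut: 2 × 0.25 × 2.8² / 0.01 = 392.
- Not consistent with 784: one-sided testing at 44–45% (616 to 618), continuity correction at those rates (822 to 824), or a relative 10% change from 44% (about 2,015 per arm).

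So 784 is right as a number analysed, for an absolute 10-point difference near the middle of the scale.

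**2. Reproduce 1,513.** 784/(0.74 × 0.70) = 1,513.5. Forward: 1,513 × 0.74 = 1,119.6 recruited, and × 0.70 = 783.7 remaining. The invitation count works only if 784 is the number after attrition, so about 784/0.70 = 1,120 women (560 per arm) must be randomised.

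**3. Power under each reading** (45% vs 55%, two-sided 5%).

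Power = Φ{[0.10 − 1.96·√(0.5/n)] / √(0.495/n)}, with n per arm:

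- n = 274.4 (784 × 0.70 = 548.8 in total): (0.10 − 0.0837)/0.0425 = 0.385, power 65%.
- n = 392: (0.10 − 0.0700)/0.0355 = 0.844, power 80%.
- n = 560: (0.10 − 0.0586)/0.0297 = 1.394, power 92%.

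| Women randomised | 30% leave the analysis | All analysed |
|---|---|---|
| 784 | 549 analysed, 65% | 784 analysed, 80% |
| 1,120 | 784 analysed, 80% | 1,120 analysed, 92% |

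The 65% hardly depends on the base rate within the range that reproduces the plan: 44% vs 54% also gives 65%, as do 40% vs 50% and 50% vs 60%. With 549 analysed, 80% power is reached only for a difference of about 1.978/√274.4 = 0.119, or 12 points.

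**4. Invitations if nobody leaves the analysis.** 784/0.74 = 1,059.5, about 1,060.

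**The case against.** Read alone, the sample-size section is coherent: 784 is the required number, invitations are inflated to reach it, and recruitment goes on until it is reached. The abstract may simply use 784 as shorthand. With all randomised women as the denominator and intention-to-treat as the main analysis, power does not fall below 80% at either target. A condensed article may also leave the reference rate to the full protocol.

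Much of this stands. The 65% needs two things together, a stop at 784 randomised and the removal of 30% from the analysis. The missing reference rate is not an error in itself, because several rates and the maximum-variance formula all lead to about 784. The contradiction remains, however. The abstract is the only place with numbers per arm, it applies them to women offered screening, and nothing in the body corrects it. The intention-to-treat defence also leaves the 30% inflation with no function for the primary outcome, and it conflicts with the rule on discontinuers.

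A reader might infer three stronger points that the documents do not support:

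- That 80% power holds only if nobody is dropped. It does not: 1,120 randomised less 30% also leaves 784 and 80%.
- That uptake among consenting women should be about 70%. This equates attrition with not attending for the test, but attrition is not defined. On that reading 0.74 × 0.70 = 52%, which does not match the 44% in the Background.
- That recruiting until 784 remain makes the sample size depend on the primary outcome. This rests on the same equation and fails if attrition means something else, such as withdrawal.

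**Conclusion.** The plan is wrong as written: it gives two incompatible randomisation targets, 784 and about 1,120, which differ by 336 women, and an end to recruitment that is tied to neither. The documents do not show that the trial is underpowered. Power is about 65% in the worst combination, 80% in two of the four, and 92% in the other. These figures assume an absolute 10-point difference near 45% vs 55%, a two-sided 5% test without continuity correction, and 30% attrition spread evenly over the arms. The conflict between the two targets rests only on the plan's own arithmetic and needs none of these assumptions except the stated 30%.

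**What to change.** Reconcile the abstract with the Recruitment, sample-size and primary-outcome sections. State the end of recruitment as a number randomised, and say that all randomised women are analysed for uptake from laboratory records, with no OGTT counted as no uptake. Suggested wording for the sample-size section:

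> 784 women will be randomised (392 per arm) and all will be analysed. This gives 80% power for an absolute difference of 10 percentage points in uptake, at about 45% versus 55%, two-sided 5%. No attrition allowance is made, because a randomised woman without a test counts as no uptake. About 1,060 women will be invited, at 74% consent. Recruitment ends when 784 women have been randomised.

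The rule on discontinuers must then be amended so that their laboratory record still counts for uptake. Without that change, dropping the attrition allowance is not safe.

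If discontinuers will instead be excluded, either state that 784 is the analysed number and about 1,120 are randomised, or keep 784 randomised and restate power as about 65%.

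Cost: the first option is a change of wording, with no more women than the abstract already gives and about 453 fewer invitations (1,513 − 1,060). Randomising 1,120 means 336 more women than the abstract states, but the same 1,513 invitations as now planned.
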